##### Online Mass Media

Parents will be recruited through social media and two smoking cessation websites, including the Dutch national smoking cessation website. With respect to social media, multiple paid Facebook advertisements will be created and used for several months. The advertisements will target on parents who are interested in smoking (cessation). Both format and message of the advertisements can differ, depending on what message and/or format will be more successful in recruiting parents who smoke. Whether advertisements are successful or not will be based on the click through ratio (i.e., the ratio of users who click on the Facebook ad of the total users who view the ad) and the costs per click on the ads. Parents who will be recruited through online mass media have to complete a short registration form (i.e., name, telephone number, and e-mail address) on the website of SineFuma so that they can be called by the coaches within one week. Parents who will fulfill the inclusion criteria will be given a description of the study. Parents who will not fulfill the inclusion criteria will not be included in the study, but they will be offered telephone counseling. Parents who will be willing to participate in this study will receive a registration form and will be asked to return the completed form (active informed consent) by mail or online on the study website.

#### 2.2.2. Health Care Approach

General health care and youth health care professionals (henceforth referred to as health care professionals) will be recruited using multiple methods, e.g., word of mouth among health care professionals and social media (i.e., Facebook and LinkedIn). Participating health care professionals will receive materials to be used for support. When smoking parents come to see a health care professional, they will be asked whether they want to receive effective smoking cessation support and whether they want a smoking cessation coach to call them. When parents give their permission, health care professionals will be able to register them online by telephone or by fax. Subsequently, professional counselors of SineFuma will contact these parents within one week. The registration process for the study will be identical to the registration process through online mass media.

### 2.3. Inclusion Criteria

To participate in the RCT, parents will have to: (1) be a parent/caretaker of a child between 0 and 18 years old; (2) be at least a weekly smoker; (3) have the intention to quit smoking currently or in the future; and (4) give informed consent to participate. Pregnant women will be excluded, and telephone counseling will be offered. The ethics committee of the Trimbos Institute has approved this study’s protocol (201607_52-1606).

### 2.4. Study Conditions

After giving informed consent and completing the baseline assessment, parents will be randomly assigned to one of the two trial conditions, telephone counseling condition or control condition.

#### 2.4.1. Telephone Counseling Condition

In the telephone counseling condition, parents will receive up to six proactive counseling phone calls (20 min) over a period of 10 weeks. The telephone counseling is based on Motivational Interviewing (MI), which is “a directive, client-centered counseling style for eliciting behavior change by helping clients to explore and resolve ambivalence” [43]. It aims to motivate patients to change, to focus on the changes that are most important to them, and to focus on their strengths instead of weaknesses and problems [44]. MI has been widely used for smoking cessation programs, and it has proven effective for smoking cessation support [45,46].

The telephone counseling will be performed by professional smoking cessation counselors of SineFuma who are thoroughly trained, experienced, and certified in delivering telephone counseling to support smoking cessation. During the six calls, multiple topics will be discussed, including information about nicotine replacement therapy, personal motivation and smoking history, preparation for the quit date, withdrawal symptoms, craving, relapse prevention, weight gain, and having a smoke-free future. Since the smoking cessation coaches will book individual appointment with parents at times that suit them, uptake will be maximized and drop-outs will be minimized. The results of Schuck et al., 2014 [14] showed that in the telephone counseling condition 224 parents (87.5%) indicated receiving at least one counseling call and 212 (82.8%) indicated receiving at least three calls. Of parents who received calls, the mean number of calls received was 5.5 (SD = 1.8). In addition, all parents will receive a supplementary brochure on smoking cessation, which was designed for this study as supplementary material for parents. The brochure (Rookvrije Ouders (Smoke-free Parents)) consists of 22 pages (color-printed, size: 30 × 21 centimeters) and provides didactic information about smoking that is relevant to parents (e.g., information about ETS) as well as exercises, motivational messages, and tips that are relevant to parents who want to quit smoking. To guarantee quality and comprehensibility of the brochure, professional counselors of SineFuma and communication experts were involved in the development of the brochure. Parents will receive this brochure by mail immediately after the start of the telephone counseling.

#### 2.4.2. Control Condition

Parents in the control condition will receive a self-help brochure on smoking cessation within one week after completing the baseline assessment. The brochure (‘Wat je zou moeten weten over stoppen met roken’ (‘What you should know about smoking cessation’)) is a 16-page, color-printed booklet (size: 30 × 21 centimeters) developed by the Trimbos Institute. The brochure includes elements that have shown to be effective, such as using positive formulation and focusing on the benefits of smoking cessation. The brochure is divided into nine parts: information about smoking and smoking addiction, deciding to quit smoking, consequences of smoking, advantages of smoking cessation, tips and exercises, available smoking cessation methods, pharmacotherapy, maintenance of smoking cessation, and physical symptoms associated with quitting smoking. Parents in the control condition will be able to receive the telephone counseling at the end of the study (i.e., when parents have completed the second assessment).

### 2.5. Data Collection

The timing of the data collection will be different for each implementation channel. Parents will be recruited gradually from September 2016 to September 2018. This means that the data of the two assessments will be obtained at different moments during the data collection (i.e., at the start of the study and at 3 months after the start of the intervention). All parents will receive a personal invitation by e-mail to complete two questionnaires online at a secured website. The web survey software application Jambo (January 2017) will be used to collect parents’ answers. At the end of the study, multiple family excursions will be raffled among parents (e.g., free entry permits for an amusement park). The parents will be told that the raffles will not be part of the parents’ incentives to enroll in the study, but to complete the two online questionnaires.

### 2.6. Randomization

An independent member of the research group will conduct randomization using a computer-generated allocation sequence. Parents will be stratified by educational level (i.e., low: no high school diploma/no vocational training; medium: vocational training or high school diploma; high: college degree), implementation channel (i.e., primary schools, health care, youth health care, and online mass media), and number of cigarettes smoked per day (i.e., less than 10; 10–20; 21 or more). When both parents live in the same household and participate in this study, randomization will be carried out at household level to avoid contamination between the two conditions.

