#### 2.2.1. Mass Media Approach

##### Primary Schools

A random sampling strategy will be used to recruit smoking parents through their children’s primary schools across all 12 provinces of The Netherlands. The randomly selected primary school boards will be asked to (1) distribute invitation letters to all children (aged 4–12 years) and ask children to hand these letters to their parents or (2) send the letters directly to the parents via e-mail. The primary schools decide which option they prefer. The invitation letters, which are targeted on parents in general and not personalized, will include a description of the study’s purpose, frequency of the assessments, and inclusion criteria. Smoking parents recruited via primary schools will be able to register for the study by completing the registration form (active informed consent) on the study website or by returning the form via mail. After the completion of the registration form, the parents will be called by professional counselors of SineFuma (one of the Dutch certified quit lines). During this phone call conversation, parents will receive additional information about the study (e.g., parents who will be randomized to the telephone counseling might have to pay for the telephone counseling (based on the parents’ health insurance), whereas parents who are randomized to the control condition do not have to pay for their intervention) based on which they will either confirm or withdraw their registration.

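### A co-resident partner who registers after the first parent is randomised inherits an arm that is probably already known, so that partner's entry is not concealed

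*Protocol article*

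**What the plan says.** Section 2.6 (Randomization) provides for couples: "When both parents live in the same household and participate in this study, randomization will be carried out at household level to avoid contamination". The same section sets the strata at the level of the parent: "Parents will be stratified by educational level", together with implementation channel and cigarettes smoked per day.

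Section 2.4 (Study Conditions) gives the order of events: "After giving informed consent and completing the baseline assessment, parents will be randomly assigned to one of the two trial conditions". Section 2.5 (Data Collection) gives the time span: "Parents will be recruited gradually from September 2016 to September 2018". Section 2.3 (Inclusion Criteria) admits parents as individuals. It contains no condition about a partner who is already in the trial.

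The arms are easy to tell apart. Section 2.4.1 provides up to six calls over 10 weeks. Section 2.4.2 provides a brochure within a week of baseline, with counselling available after the second assessment. Section 2.2.1 (Primary Schools) adds that "parents who will be randomized to the telephone counseling might have to pay for the telephone counseling", while control parents do not pay. Parents confirm or withdraw their registration on the basis of that information.

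**The concern.** The household rule serves a good purpose, which is to stop contamination between partners. It protects concealment only if both partners are committed before the household is allocated. Under gradual recruitment one parent can be randomised and begin the assigned condition, and the other can register weeks or months later. The second parent's arm is then already settled and probably known to that parent when deciding whether to consent.

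The arms differ in ways that could affect that decision: personal calls or a brochure, a possible charge in one arm only, and counselling now or after the second assessment. If late partners join one arm more readily than the other, or different kinds of partner join each arm, the groups are no longer comparable by randomisation. Section 2.10 relies on intention-to-treat. That principle keeps everyone in the arm assigned, but it cannot undo selection that took place before entry.

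**Working it through.** **1. What happens to a late partner.** Sections 2.4, 2.5 and 2.6 leave two possibilities when the second parent registers after the first has been randomised.

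- The partner takes the household's existing arm. This follows section 2.6, but the allocation was made before the partner consented and is visible at home.
- The partner is randomised separately. This keeps the allocation concealed, but the two parents may land in different arms, which breaks section 2.6 and defeats its stated aim of avoiding contamination.

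The article states no third course, such as leaving the late partner out of the comparison.

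**2. Size.** The plan gives no figure to reproduce here: no number of couples, of late partners, or of their quit rates. The following shows scale only.

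- From section 2.7: 36 per arm in each of two approaches, so 36 × 2 = 72 per arm. Control quit rate 12.1%; design difference 44.5 − 12.1 = 32.4 points.
- Assumed, with no source: counselling has no effect, so both arms quit at 12.1%; n = 8, 12 or 20 late partners; these partners quit at 30%; all join one arm.
- Rate in the arm they join: (72 × 0.121 + n × 0.30) / (72 + n), where 72 × 0.121 = 8.712.

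| n | Calculation | Rate | Shift from 12.1% |
|---|---|---|---|
| 8 | (8.712 + 2.4) / 80 | 13.9% | 1.8 points |
| 12 | (8.712 + 3.6) / 84 | 14.7% | 2.6 points |
| 20 | (8.712 + 6.0) / 92 | 16.0% | 3.9 points |

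**3. Direction.** In general the shift in the arm joined is n / (72 + n) × (q − 0.121), where q is the late partners' own quit rate.

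- If they join the counselling arm and q exceeds 12.1%, the bias favours counselling.
- If they join the control arm instead, the same numbers favour control by 1.8 to 3.9 points.
- If q is below 12.1%, the sign reverses again.
- If 20 join counselling and 8 join control, all at 30%, the net shift is 3.9 − 1.8 = 2.1 points.
- If equal numbers with the same q join both arms, there is no shift.

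The document fixes neither the arm that late partners would prefer nor q.

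**4. Strata.** Three education levels, four channels and three smoking levels give 3 × 4 × 3 = 36 cells, or 158 / 36 = 4.4 parents per cell on average. Partners who differ on any factor belong to two cells, and the article does not say which one the household takes. Naming one parent as the reference settles it, so both rules can be applied.

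**The case against.** The strongest reply is that this is a condensed article stating a principle. Its natural reading is that a couple taking part is randomised as one unit. What happens to a partner who appears later is procedural detail that a full protocol may cover, and that such a partner joins knowing the arm is an inference. Part of this stands: a fuller rule may exist, and knowledge of the arm is probable rather than certain. It does not remove the point, because the rule as printed, combined with the stated order of events and the two-year window, itself leads to unconcealed entry.

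A reader might infer that the bias must favour counselling. The document does not support that. Counselling may carry a charge, which could deter partners. Controls can have counselling after the second assessment, so the brochure is not all they will ever be offered. Online registrants who do not meet the criteria are offered counselling anyway, so the trial is not the only route to it. Late registrants might also be less motivated than the parents who came first.

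A reader might also infer that the household rule and the stratification rule contradict each other. They do not. A discordant couple lacks a tie-break, which any reference-parent convention supplies, and the choice affects balance for a few couples without biasing the comparison.

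Finally, the illustrated shifts rest on invented partner counts and an invented quit rate, and they are small beside 32.4 points. That objection stands in full.

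**Conclusion.** The point holds in limited form. As written, section 2.6 allows a partner to enter the randomised comparison after the household's arm has been set and is probably known, so concealment fails for that partner and selection at entry becomes possible. This rests on two assumptions: that some couples enrol one after the other, and that the first parent's condition is evident at home.

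The direction of any bias is unknown. Its size cannot be estimated from the document and is probably small. The 1.8 to 3.9 point shifts show scale under assumed inputs and are not an estimate. The correction is still worth making, because the weakness lies in the entry rule, analysis by assigned arm does not remove it, and closing it costs little. The unstated stratum for discordant couples is a minor clarification only.

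**What to change.** Add to section 2.6 that a co-resident partner is counted in the randomised comparison only if that partner has consented and completed the baseline assessment before the household is randomised. Partners who register later are left out of the trial outcomes and do not count towards the 158. This concerns only who is counted; it takes no position on what support a late partner is offered.

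A question at registration about a smoking partner who also wishes to take part would let most couples enter together. In the same section, name the parent whose education, channel and smoking level place the household in a stratum, for example the one who registered first.

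The cost is a sentence or two in the plan, one registration question, and the loss of a few late-registering partners from the count. The protection against contamination within households is kept.

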### 2.7. Sample Size

Based on the results of Schuck and colleagues (2014) [14], our power calculation (Stata 12.1, StataCorp., College Station, TX, USA) indicated that 72 parents per implementation approach (36 intervention and 36 control) is sufficient to detect 7-day prevalence abstinence at three months post-intervention with a large effect (*p*_1_ = 0.445, *p*_2_ = 0.121, Power = 0.80, α = 0.05). Because we want to examine differences in smoking cessation rates between the two implementation approaches, we have to double from 72 to 144 parents. Based on the drop-out rates at 3-month follow-up of Schuck et al., 2014 [14] (i.e., 10% in the control group and 3.9% in the intervention group), we will anticipate 10% drop-out. This means that we will aim to recruit a minimum of 158 participating parents in total.

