### 2.9. Economic Evaluation

The present study examines the cost-effectiveness of the telephone counseling in accordance with the CHEERS checklist [48]. Four types of costs will be considered: (1) the costs of offering the interventions; (2) recruitment costs for each implementation approach and channel; (3) costs stemming from health care uptake; and (4) costs stemming from losses in productivity, in both paid work and volunteer jobs. Costs of the interventions and implementation channels and approaches (e.g., sending materials to health care professionals and advertisements on Facebook) will be monitored during the study. Other costs will be calculated by using standard cost prices (for reference year 2014), which are published in the Dutch guideline for costing [49]. The data on costs stemming from health care uptake and losses in productivity will be collected using the Trimbos/iMTA Questionnaire on Costs associated with Psychiatric illness (TiC-P) [50]. The TiC-P is the most widely used patient-reported measure of health service utilization in The Netherlands [51]. The cost-effectiveness analyses (CEA) will be conducted along the RCT, with 7-day point prevalence abstinence at three months post-intervention as the primary outcome (i.e., the incremental effect). The incremental costs will be calculated as the average cost difference between the conditions. Both the incremental effect and incremental costs will be combined to compute the incremental cost-effectiveness ratio (ICER; incremental costs/incremental effects). To manage stochastic uncertainty, 2500 non-parametric bootstraps will be used and the bootstrapped ICERs will be plotted on the ICER plane. Based on the four quadrants of the ICER plane, four scenarios are possible regarding the telephone counseling, which can: (1) costs more and be more effective; (2) costs more and be less effective; (3) costs less and be less effective; and (4) costs less and be more effective. As seen from a health-economics perspective, the second and fourth scenarios are clear cut cases for decision-makers, with the second scenario being the least attractive (and the intervention is dominated by its alternative (the self-help brochure)) and the fourth scenario being the most attractive, and decision-makers will opt for the intervention. On the other hand, the first scenario is more difficult for decision-makers. In this scenario, one needs to decide how much one is willing to pay for an additional unit of effect (one extra parent who was successful in refraining to smoke) [52]. To facilitate this decision, an ICER acceptability curve will be plotted with the probability that one deems the intervention to be cost-effective (on the *y*-axis) against various willingness-to-pay ceilings (on the *x*-axis). Finally, the CEA will be completed by performing one-way sensitivity analyses directed at uncertainties in major cost-drivers. This is done to ascertain the robustness of the CEA findings.

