
### 2.10. Statistical Analyses

Statistical analyses will be carried out to assess whether the randomization results in an equal baseline distribution of relevant participant characteristics across conditions. In case of group differences at baseline, confounding variables will be included in subsequent analyses. All analyses will be conducted in accordance with the intention-to-treat principle (i.e., all parents randomized to one of the two conditions will be included in the analyses examining the study hypotheses) as per the Consolidated Standards of Reporting Trials [53]. Moreover, a completers-only analyses will be conducted, i.e., only parents with outcome data on all assessments will be included in the analyses. To compare cessation rates across different groups, logistic regression analyses will be conducted. In addition, Mplus will be used to test for moderation and subsequently, multi-group testing with bootstrapping will be conducted to assess differences between recruitment approaches. Effect sizes and 95% confidence intervals (CI) will be reported to determine the magnitude and effect of the intervention.

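### Couples are randomised as one household, but the sample size assumes independent parents and the named analyses make no provision for household; the effect is small unless couples are common

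*Protocol article*

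**What the plan says.** Section 2.6 makes the household the unit of allocation for couples: "When both parents live in the same household and participate in this study, randomization will be carried out at household level". The reason given is to prevent contamination between conditions.

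Section 2.7 counts in parents: "72 parents per implementation approach (36 intervention and 36 control) is sufficient", with inputs "0.445, *p*_2_ = 0.121, Power = 0.80, α = 0.05". Then "we have to double from 72 to 144 parents" and "we will anticipate 10% drop-out", giving a target of 158. No design effect and no expected number of couples appear.

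Section 2.10 names the method for the outcomes: "To compare cessation rates across different groups, logistic regression analyses will be conducted". It adds moderation testing in Mplus and a multi-group comparison with bootstrapping. In section 2.9, "2500 non-parametric bootstraps will be used" for the cost-effectiveness analysis. Neither section mentions household, clustering, robust errors or the unit that is resampled. The inclusion criteria in 2.3 do not limit enrolment to one parent per household.

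**The concern.** Two partners who enrol together always get the same condition and share a home. If one stops smoking, the other is plausibly more likely to stop, so their outcomes tend to be positively correlated within an arm. An analysis that counts them as two separate observations then takes the information to be greater than it is. Standard errors come out too small, the type I error of the primary comparison rises above 5%, and the cloud of bootstrapped cost-effectiveness ratios is too tight.

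The article fixes the allocation unit, the sample size and the analysis methods, and the last two do not follow the first. The point is sharpest for outcomes that partners share. Home smoking restrictions are a secondary outcome (2.8), and two parents in one home report on the same rules.

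**Working it through.** **1. Reproduce the sample size (2.7).** Inputs: p1 = 0.445, p2 = 0.121, power 0.80, α = 0.05, equal arms ("36 intervention and 36 control"). Sidedness is not stated; two-sided is used here.

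- Difference d = 0.324; mean rate = (0.445 + 0.121)/2 = 0.283.
- Uncorrected n per arm = {1.960 × √(2 × 0.283 × 0.717) + 0.842 × √(0.445 × 0.555 + 0.121 × 0.879)}² / d² = (1.2486 + 0.5003)² / 0.1050 = 29.1, so 30.
- With continuity correction: n = (29.1/4) × {1 + √(1 + 4/(29.1 × 0.324))}² = 35.04, so **36**, as stated.
- 2 × 36 = 72 per approach; 2 × 72 = 144; 144 × 1.10 = 158.4, stated as 158.

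The stated figure is therefore the formula for independent observations, with a design effect of 1. That it holds no household allowance is shown by the reproduction and need not be inferred from silence.

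**2. Design effect.** Let f be the share of parents enrolled as couples and ICC the within-couple correlation of the outcome. Clusters have size 1 or 2, so Σm²/Σm = (1 − f) × 1 + f × 2 = 1 + f, and the design effect is DE = 1 + f × ICC. The correct interval is √DE times as wide as the naive one. The naive 95% interval covers 2Φ(1.96/√DE) − 1. The article gives neither f nor ICC, so all values below are assumptions.

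| f | ICC | DE | Correct interval wider by | Coverage of naive 95% interval | Parents needed to match 144 independent |
|---|---|---|---|---|---|
| 0 | any | 1.000 | 0% | 95.0% | 144 |
| 0.05 | 0.3 | 1.015 | 0.7% | 94.8% | 147 |
| 0.1 | 0.5 | 1.05 | 2.5% | 94.4% | 152 |
| 0.2 | 0.5 | 1.10 | 4.9% | 93.8% | 159 |
| 0.2 | 1.0 | 1.20 | 9.5% | 92.6% | 173 |
| 0.5 | 0.5 | 1.25 | 11.8% | 92.0% | 180 |

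Type I error is 100% minus the coverage: 6.2% at DE = 1.10, for example. The row with ICC = 1.0 stands for an outcome that the household fully shares, as home smoking rules nearly are.

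**3. Power.** The effective number per arm is n/DE.

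| DE | Per approach, 36 per arm, continuity-corrected | Per approach, uncorrected | Overall, 72 per arm, continuity-corrected |
|---|---|---|---|
| 1.000 | 81.3% | 87.9% | 99.0% |
| 1.015 | 80.6% | 87.4% | 98.9% |
| 1.05 | 78.9% | 86.2% | 98.6% |
| 1.10 | 76.5% | 84.6% | 98.2% |
| 1.25 | 69.5% | 79.5% | 96.5% |

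By the formula that reproduces 36, power per approach drops below 80% between DE = 1.015 and DE = 1.05. The overall comparison keeps ample power throughout.

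**The case against.** Four arguments weigh against the point.

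- **The article does not say that parents are analysed as independent.** A reader might infer this from the named methods, but 2.9 and 2.10 leave the variance estimator and the resampling unit open. A logistic regression with household-robust errors is still a logistic regression, and a bootstrap of households is still non-parametric. A separate analysis plan may settle both. This stands, so the point can only be that no provision is made. It does not reach 2.7, where the independence assumption is built into the stated number.
- **Too-narrow intervals are not established.** A reader might conclude that the intervals are bound to be too narrow. That requires couples to enrol and partners' outcomes to be positively correlated, and the documents quantify neither. Section 2.6 covers a contingency. Online recruitment and health care referral (2.2) reach parents largely one at a time. School letters could reach both partners, but the Introduction reports a 5% response through schools in the earlier efficacy study. This stands: the conclusion is conditional.
- **Clusters hold at most two parents, so the effect is small.** This stands for f up to 0.2 and ICC up to 0.5, where correct intervals are up to about 5% wider. It is weaker for outcomes that the household shares.
- **The trial is not underpowered.** A reader might infer that it is. The overall comparison has 96.5% power even at DE = 1.25 under the assumed effect, so this stands for that comparison. Power per approach, on which the doubling to 144 rests, has little margin by the formula that gives 36.

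**Conclusion.** The mismatch is real and minor. Couples are allocated as households, the sample size is shown to assume independent parents, and the named analyses do not carry the household forward. Followed as written, the plan understates uncertainty to the extent that couples enrol and their outcomes are positively correlated.

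At assumed values from f = 0.05, ICC = 0.3 to f = 0.2, ICC = 0.5, the design effect runs from 1.015 to 1.10. The understatement is larger only if couples make up much of the sample, or for shared outcomes such as home smoking restrictions. If no couples enrol, nothing changes. The documents do not support saying that the plan asserts independence in the analyses, that its intervals are necessarily too narrow, or that the main comparison lacks power.

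**What to change.** - **Section 2.10:** for primary and secondary outcomes, use household-clustered standard errors, or GEE logistic regression with household as the cluster. Declare household as the cluster in Mplus.
- **Sections 2.9 and 2.10:** resample households instead of parents in the economic bootstrap and in the multi-group bootstrap.
- **Section 2.7:** add that the 80% power per approach at 36 per arm assumes independent parents and is somewhat lower if couples enrol.

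The cost is a household identifier in the data set, a few options in the analysis code and a few sentences. Intervals become slightly wider if couples enrol and are essentially unchanged if none do. The recruitment target need not change for the overall comparison.
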